## Introduction

Unstable Angina (UA) is a critical subtype of Acute Coronary Syndrome (ACS) with high incidence and disability rates globally. In China, approximately 2.5 million new ACS cases are reported annually, with over 40% being UA, a figure expected to rise due to aging demographics and lifestyle changes. Although Percutaneous Coronary Intervention (PCI) effectively alleviates ischemic symptoms in UA patients, issues such as restenosis, recurrent cardiovascular events, and poor long-term prognosis remain significant. Studies show that the incidence of major adverse cardiovascular events (MACEs) within the first year post-PCI can reach 10%-15%, closely linked to patients' heart function, lifestyle, and adherence to rehabilitation management. Therefore, improving the long-term outcomes of UA patients post-PCI through effective cardiac rehabilitation (CR) interventions has become a vital aspect of secondary prevention in cardiovascular disease.

Traditional CR programs, encompassing exercise, risk factor management, and psychological support, have proven effective in reducing cardiovascular mortality and improving life quality. However, challenges such as low participation rates (<30%), regional disparities, and difficulties in long-term follow-up limit their widespread application. Recently, mobile health technologies (mHealth)-based remote CR have gained popularity, offering personalized, real-time guidance via smartphones, wearables, and remote monitoring systems. Initial studies suggest mHealth CR can improve physical endurance (e.g., a 15%-20% increase in 6-minute walk test) and reduce 30-day readmission rates. However, its efficacy, long-term effects, and safety in UA patients post-PCI remain underexplored.

This study aims to assess the effectiveness of a multidimensional mHealth-based cardiac rehabilitation program for UA patients undergoing PCI. Specific objectives include (1) comparing quality of life scores between the mHealth intervention and usual care groups at 6 months post-PCI, (2) exploring the impact of mHealth on patient adherence, self-management, and psychological well-being, and (3) providing evidence-based recommendations to optimize post-PCI rehabilitation strategies for UA patients and promote the clinical application of digital health technologies in

cardiovascular rehabilitation.

## **Methods**

### **Study Rationale**

The multidimensional digital cardiac rehabilitation intervention package used in this study was developed by the Department of Cardiology at the First Affiliated Hospital of Bengbu Medical University, specifically designed for the rehabilitation of patients with unstable angina (UA) who have undergone percutaneous coronary intervention (PCI). This intervention package is based on mHealth technology, offering the following advantages: it facilitates remote, personalized health management through a digital platform, overcoming the temporal and spatial limitations typically encountered in traditional cardiac rehabilitation. mHealth technology provides convenient remote guidance, ensuring that patients receive continuous and individualized support throughout their rehabilitation process. Particularly in terms of visualization, mHealth technology utilizes videos, images, and animations, helping patients intuitively understand rehabilitation content, accurately master exercise techniques, and treatment plans, thereby enhancing adherence and reducing the risk of errors. Through this interactive educational model, patients are better able to engage in the rehabilitation process, promoting improved treatment outcomes.

The intervention package integrates seven core dimensions: exercise training, medication management, nutrition guidance, psychological support, sleep management, health education, and smoking cessation support, aiming to provide patients with a comprehensive and personalized rehabilitation plan. All content was collaboratively developed by cardiologists, rehabilitation physicians, and nurses to ensure the professional quality and clinical feasibility of the program. The intervention package is delivered through a digital platform in various formats, including videos, images, and animations, enabling patients to access rehabilitation guidance and support through mobile devices during hospitalization and after discharge. We employed frame-by-frame animation technology to design exercise programs, ensuring that each patient's physical capacity and needs are addressed, thus

improving exercise adherence and avoiding the risks of overtraining.

The advantage of the multidimensional digital cardiac rehabilitation intervention package lies in its ability to provide personalized interventions tailored to each patient's specific condition, encompassing multiple aspects such as exercise, medication management, and nutrition guidance. The exercise training design not only helps improve cardiovascular function but also enhances muscle endurance, restoring the patient's ability to perform daily activities. The medication management dimension ensures that patients take their medications correctly and on time, reducing the occurrence of adverse drug reactions. Nutrition guidance assists patients in managing their weight and lowering blood lipids through appropriate dietary interventions, thus reducing the risk of cardiovascular disease recurrence. Psychological support, sleep management, and smoking cessation support help patients overcome the psychological stress caused by illness, improve sleep quality, and eliminate unhealthy lifestyle habits. These integrated interventions effectively improve the patient's overall health and contribute to the long-term maintenance of cardiovascular health.

Furthermore, this study places particular emphasis on the implementation of prehabilitation training, starting during hospitalization, which allows patients to become familiar with standardized rehabilitation content early on. During this process, the patients' family members were also included in the rehabilitation training program, ensuring they can provide essential support and enhance the role of health education within the home environment. These interventions collectively contributed to improvements in the patients' physical function, frailty, and lipid levels, while also enhancing their mental health and quality of life.

From a clinical application perspective, the digital rehabilitation package not only overcomes the temporal and spatial limitations of traditional inpatient treatment but also provides continuous and personalized rehabilitation support. Even after discharge, patients can continue to receive rehabilitation education, engage in self-management, and stay in contact with the medical team through the digital platform. This model is particularly beneficial for patients living in areas with limited access to medical

resources or those unable to attend regular outpatient treatments due to work or lifestyle factors. Moreover, the digital rehabilitation package enables real-time monitoring of the patient's rehabilitation progress, facilitating timely adjustments to treatment plans and ensuring optimal rehabilitation outcomes. Through this digital intervention model, we can significantly improve patient adherence to rehabilitation and treatment outcomes, providing a feasible practical solution for the future of digital health management.

## **Study Purpose**

**Primary Objective:** To assess improvement in 6-minute walk test (6MWT), 12-item Short Form Health Survey (SF-12) scores, and frailty phenotypic scores in UA patients undergoing PCI at 3 months postoperatively.

**Secondary Objectives:** To evaluate the changes in gait speed, 30-second chair stand test (30-s CST), grip strength, waist circumference (WC), body mass index (BMI), total cholesterol (TC), high-density lipoprotein cholesterol (HDL-C) levels, low-density lipoprotein cholesterol (LDL-C) levels, and triglycerides (TG) levels were assessed three months after PCI in patients with UA.

## **Study Design**

In this prospective, emulated target trial, we aim to evaluate the effectiveness of multidimensional digital cardiac rehabilitation in UA Patients undergoing PCI. In this study, the process of patient recruitment began when patients were diagnosed with unstable angina (UA), which was implemented in the First Affiliated Hospital of Bengbu Medical University. Potential participants were identified from the hospital's PCI registry, which included all patients with ACS requiring PCI. During this process, the research team conducted a detailed pre-screening process to ensure that patients met the inclusion criteria. The pre-screening criteria included: patients should be diagnosed with unstable angina and planned to undergo percutaneous coronary intervention (PCI); the patient's age, the stability of their condition and their ability to actively cooperate with rehabilitation training and related interventions were also used as part of the screening criteria. Patients who meet these criteria will be enrolled in the study to receive further health assessment and individualized interventions.

143 The research team recruits patients at the time of admission through the  
144 hospital's multimedia ward. The recruitment process is handled by a research team  
145 comprised of healthcare professionals from both the cardiovascular and rehabilitation  
146 departments, including attending physicians, nurses, rehabilitators, and research  
147 assistants, who provide patients with a detailed introduction to the study and an  
148 explanation of the intervention protocol during admission.

149 To ensure that patients understand the content of the study and the requirements  
150 for participation, the hospital is specially equipped with multimedia equipment,  
151 including video, graphic and animation displays, to help patients visualize the purpose  
152 of the study, the intervention protocol and the various study requirements. Through  
153 this multimedia ward environment, patients can receive comprehensive information  
154 about the study in a relaxed atmosphere, thus increasing their acceptance of the study  
155 and willingness to participate.

156 In addition, the research team has prepared relevant study materials and informed  
157 consent forms in advance to ensure that each patient is fully aware of his/her  
158 participation and related rights and interests before participating in the study. The  
159 research team will ensure that patients have signed the informed consent form before  
160 entering the study and will provide ongoing support and guidance throughout the  
161 study.

162 After the recruitment and pre-screening processes, patients were divided into two  
163 groups based on their admission dates: the control group (April to May 2022) and the  
164 intervention group (May to June 2022). In addition to receiving standardized  
165 treatment, the intervention group also received a multidimensional digital cardiac  
166 rehabilitation intervention, which encompassed seven dimensions: exercise training,  
167 medication management, nutritional guidance, psychological support, sleep  
168 management, health education, and smoking cessation support. It is important to note  
169 that, in addition to the intervention for patients themselves, the digital cardiac  
170 rehabilitation intervention particularly emphasized the involvement of the patients'  
171 family members. During the hospitalization period, family members were invited to  
172 participate in the rehabilitation training program, ensuring that they could provide

necessary support for the patients and promote health education within the home environment. The control group, on the other hand, received only standardized treatment and standard nursing care.

After the PCI procedure, both groups of patients underwent a three-month follow-up period. The follow-up included individualized educational sessions conducted monthly via the WeChat platform, in addition to outpatient visits at one and three months post-surgery. During the follow-up, patients were required to report their health status to the multidisciplinary intervention team, including blood pressure, physical activity, dietary habits, sleep patterns, psychological state, and progress in smoking cessation.

Only patients who completed all data collection requirements were included in the final analysis. The final dataset was subjected to propensity score matching to balance the baseline characteristics between the two groups, ensuring comparability.

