### **Study Population**

This emulated target trial was conducted at the First Affiliated Hospital of Bengbu Medical University, including 164 UA patients who underwent PCI in the Department of Cardiology from April to May 2022 (the control group) and May to June 2022 (the intervention group). Main inclusion criteria were as follows: (1) Patients diagnosed with UA who successfully underwent PCI; (2) patients classified as having cardiac function grades 1 to 3; (3) patients with no new or recurrent chest pain for at least eight hours after reperfusion therapy, no new arrhythmias or ECG changes within this timeframe, and no further elevation in myocardial injury marker levels; (4) patients capable of using a smartphone; and (5) patients who understood the purpose of this study and voluntarily provided written informed consent. The exclusion criteria were as follows: (1) patients with significant postoperative wound bleeding, severe infection, fever, severe electrolyte–acid–base imbalance, severe

hypoxia, or malnutrition; and (2) patients who were unwilling to participate in this study or unable to adhere to the follow-up visit requirements.

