### **Randomization**

Owing to the nature of the intervention, the participants were not randomly assigned. To minimize potential confounding factors, the multidimensional digital cardiac rehabilitation intervention group and the usual care group were matched on the basis of propensity scores calculated using logistic multiple regression analysis. The matching process involved considering covariates such as age, sex, education level, marital status, exercise habits, monthly salary, current address, living arrangement

(solitary or not), history of CHD, history of PCI, length of hospitalization, medical insurance status and polypharmacy data obtained from presurveys. Propensity score analysis was conducted using a 1-to-1 ratio matching approach with the nearest neighbour method to ensure balanced characteristics between the intervention and control groups. A standard calliper width of 0.2 was used for the propensity score. After matching, a total of 136 patients were included, with 68 patients in the multidimensional digital cardiac rehabilitation group and 68 patients in the usual care group.

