### **Study Outcome**

All clinical outcome measurements were obtained at the three-month follow-up. The primary outcomes included differences in the 6MWT, the SF-12 scores, and the frailty phenotype scores. Secondary outcomes comprised step speed, 30s-CST, grip strength, WC, BMI and changes in lipid profiles (TC, HDL-C, LDL-C, and TG) at 3 months.

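### The analysis keeps only patients who completed all data collection and then matches them, which leaves the 3-month group difference open to selection bias of unknown size and direction

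*Combined protocol and SAP*

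**What the plan says.** - **Analysis set and order of steps.** Study Design says "Only patients who completed all data collection requirements were included in the final analysis" and continues directly: "The final dataset was subjected to propensity score matching to balance the baseline characteristics between the two groups, ensuring comparability". The completer restriction therefore comes first and the matching second. What counts as complete is not defined. The required visits also differ within the document: Study Design has outpatient visits at one and three months, while Post-Discharge Rehabilitation names only the third month.
- **Timing of outcomes.** Study Outcome: "All clinical outcome measurements were obtained at the three-month follow-up".
- **Allocation.** Randomization: "Owing to the nature of the intervention, the participants were not randomly assigned". Study Design forms the groups by admission date.
- **Analysis.** Statistical Method lists t, Wilcoxon, chi-square and Fisher tests. It gives no missing-data method, no analysis of all enrolled patients and no sensitivity analysis.
- **Counts.** Study Population and Results give 164 patients (89 intervention, 75 usual care) before matching. Randomization and Results give 68 per arm afterwards. Neither place says whether 164 means enrolled or completed.
- **Entry and timing.** Study Design: "The research team recruits patients at the time of admission through the" hospital's multimedia ward, with PCI still planned. Study Rationale: "this study places particular emphasis on the implementation of prehabilitation training, starting during hospitalization". Study Duration runs the programme throughout the hospital stay. Study Population, however, requires a successful PCI and "patients with no new or recurrent chest pain for at least eight hours after reperfusion therapy". It also excludes patients "unable to adhere to the follow-up visit requirements", without saying when that is judged.

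**The concern.** Whether a patient completes three months of data collection is known only after the programme has begun. Conditioning on it selects both arms on something the programme, or the patient's course, may have influenced. The listed matching covariates are demographic, social and history variables, together with length of hospitalization. They can balance the completers on those characteristics, but they cannot bring back patients removed for later events.

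The document itself gives grounds to expect incomplete follow-up. Its Introduction cites major cardiac events in 10% to 15% of patients in the first year after PCI, rehabilitation participation below 30%, and difficulty with long-term follow-up. Completion could differ by arm in either direction. The intervention arm has more contact and family involvement, which may help retention; it also carries more demands, which may harm it. With no randomisation, the comparison has no other protection.

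The rule governs all three primary outcomes (6MWT, SF-12, frailty phenotype). Death and readmission are not among the listed outcomes, so a patient lost for either reason would not enter the comparison at all.

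**Working it through.** **1. The plan's own counts reproduce.** 89 + 75 = 164; 68 + 68 = 136; 59/136 = 43.38% female. Matching removed 164 − 136 = 28 patients (17.1%): 21 of 89 intervention (23.6%) and 7 of 75 usual care (9.3%). These are matching losses. The number lost to the completer rule is not in the readable text. If 164 are the completers, an assumed loss of 0% to 20% implies between 164 and 164/0.8 = 205 enrolled.

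**2. Precision.** In outcome SD units, with 68 per arm and treating the arms as independent, SE = √(2/68) = 0.171. The difference detectable with 80% power at two-sided 5% is (1.96 + 0.84) × 0.171 ≈ 0.48 SD. The plan does not state sidedness; two-sided is assumed.

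**3. Bias, first model (assumed losses).** Let d be the share lost in an arm and D the mean deficit of lost patients against completers, in SD. Completers overstate that arm's mean by d × D. The bias in the difference is d₁D₁ − d₀D₀ (1 = intervention, 0 = control). With no true effect, the error rate is P(|Z + bias/SE| > 1.96).

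| Loss, intervention vs control | Deficit (SD) | Bias (SD) | Error rate |
|---|---|---|---|
| none, or equal loss with equal deficit | – | 0 | 5.0% |
| 10% vs 5% | 0.5 both | 0.10×0.5 − 0.05×0.5 = 0.025 | 5.2% |
| 20% vs 5% | 0.5 both | 0.10 − 0.025 = 0.075 | 7.2% |
| 5% vs 20% | 0.5 both | 0.025 − 0.10 = −0.075 | 7.2% |
| 20% vs 5% | 1 both | 0.20 − 0.05 = 0.15 | 14.1% |
| 20% vs 20% | 1 vs 0 | 0.20 − 0 = 0.20 | 21.5% |

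**4. Bias, second model (assumed correlation).** Let ρ be the correlation between the tendency to drop out and a poor 3-month outcome, and q the share lost. The completers' mean is shifted by ρ·φ(z_q)/(1 − q). The factor φ(z_q)/(1 − q) is 0.109 at q = 5%, 0.195 at 10%, 0.350 at 20% and 0.497 at 30%. With ρ from 0.3 to 0.7:

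- 10% vs 5%: difference in factors 0.086; bias 0.03 to 0.06 SD; error rate 5.3% to 6.4%.
- 20% vs 10%: difference 0.155; bias 0.05 to 0.11 SD; error rate 5.8% to 9.7%.
- 30% vs 10%: difference 0.302; bias 0.09 to 0.21 SD; error rate 8.2% to 23.4%.

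Swapping the arms reverses every sign. A positive value favours the programme and arises when the intervention arm loses more patients, or sicker ones. Better retention in the intervention arm gives a negative value.

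**The case against.** The strongest reply is that no loss is documented. If all enrolled patients completed, or if losses were alike in size and kind, this bias is zero. The flowchart is not shown and may report the losses. That stands. A reader might infer from the completer rule that the result *is* biased, or that adverse outcomes are being hidden. The documents support neither inference.

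The size rests on assumption alone. The largest error rate needs 30% vs 10% loss with a correlation of 0.7, and nothing in the text supports either figure. Nor may the direction be presumed. The obvious retention mechanism, extra contact and family involvement, would bias against the programme. That mechanism is itself limited after discharge, because the one-on-one sessions belong to the in-hospital phase and Study Design gives both groups monthly WeChat sessions and outpatient visits.

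A reader might also infer that consented patients were removed for events after PCI or for not adhering. The text does not show this. The adherence criterion sits among the entry exclusions, and Study Design makes ability to cooperate part of pre-screening, so a judgement at entry is the natural reading. Prehabilitation is said to start in hospital, not before PCI, and Informed Consent places consent after a screening visit. The timing is unclear rather than proven wrong. A time zero after the eight-hour window would be as valid as one at admission, and the successful-PCI criterion need not be dropped.

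What survives is the rule itself: a stated post-baseline restriction, applied before matching, with nothing planned to offset it.

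**Conclusion.** The concern holds as a risk, not as demonstrated bias. The completer rule is explicit, it selects both non-randomised arms on a later condition, and baseline matching cannot undo that. The 3-month difference is open to selection bias whose size and direction cannot be determined from the documents.

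Over the losses tried, the bias reaches about 0.2 SD in either direction. That exceeds one standard error and is a little over 40% of the difference detectable with 80% power (0.20/0.48 = 42%). With smaller or similar losses it is slight or nil. These figures depend on assumed losses, deficits and correlations. Because the text does not say whether 164 counts enrolled patients or completers, a reader cannot rule the problem out.

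**What to change.** 1. **Analysis set.** Make the primary set all enrolled patients in both admission periods who met the entry criteria at one stated time zero, the same in both arms. Remove nobody for later events or non-completion.
2. **Reconcile the timing.** Study Rationale, Study Design, Study Duration and Study Population must agree on whether enrolment and the programme start before or after the successful-PCI and eight-hour criteria are assessed. State that ability to adhere to follow-up is judged at entry only. Define completion, and reconcile the required visits.
3. **Matching.** Fit the propensity score on that set, from data available at time zero. Length of hospitalization, known only at discharge, does not qualify if time zero falls during the stay.
4. **Missing outcomes.** Use multiple imputation, with baseline outcomes, matching covariates and group in the model, or inverse-probability-of-retention weights. Add a missing-not-at-random sensitivity analysis. Treat deaths separately: a 3-month 6MWT or SF-12 does not exist for a patient who has died.
5. **Reporting.** Give enrolled numbers, deaths, readmissions, withdrawals and reasons by arm before matching. Keep the completer analysis as a sensitivity analysis only.

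**Cost.** Revised SAP wording and a re-run, slightly wider intervals, and a stated missing-data assumption. It also relies on baseline data for non-completers. Physical fitness and lipids are recorded at admission, and Informed Consent describes database entry at screening. The 6MWT, SF-12 and frailty sections do not say whether those were measured at baseline, and completeness of the covariates is not documented.
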